## Abstract

**Background:**

Performing regular exercise is known to manifest a number of health benefits that mainly relate to cardiovascular and muscular adaptations to allow for greater oxygen extraction and utilization. There is increasing evidence that nutrient intake can affect the adaptive response to a single exercise bout, and that protein feeding is important to facilitate this process. Thus, the exercise-nutrient interaction may potentially lead to a greater response to training. The role of post-exercise protein ingestion in enhancing the effects of running-based endurance exercise training relative to energy-matched carbohydrate intervention remains to be established. Additionally, the influence of immediate versus overnight protein ingestion in mediating these training effects is currently unknown. The current protocol aims to establish whether post-exercise nutrient intake and timing would influence the magnitude of improvements during a prescribed endurance training program.

**Methods/Design:**

The project involves two phases with each involving two treatment arms applied in a randomized investigator-participant double-blind parallel group design. For each treatment, participants will be required to undergo six weeks of running-based endurance training. Immediately post-exercise, participants will be prescribed solutions providing 0.4 grams per kilogram of body mass (g · kg^−1^) of whey protein hydrolysate plus 0.4 g · kg^−1^ sucrose, relative to an isocaloric sucrose control (0.8 g · kg^−1^; Phase I). In Phase II, identical protein supplements will be provided (0.4 + 0.4 g · kg^−1^ · h^−1^ of whey protein hydrolysate and sucrose, respectively), with the timing of ingestion manipulated to compare immediate versus overnight recovery feedings. Anthropometric, expired gas, venous blood and muscle biopsy samples will be obtained at baseline and following the six-week training period.

**Discussion:**

By investigating the role of nutrition in enhancing the effects of endurance exercise training, we will provide novel insight regarding nutrient-exercise interactions and the potential to help and develop effective methods to maximize health or performance outcomes in response to regular exercise.

**Trial registration:**

Current Controlled Trials registration number: ISRCTN27312291 (date assigned: 4 December 2013). The first participant was randomized on 11 December 2013.

## Background

Performing regular exercise has a multitude of health benefits that stem from cardiovascular and skeletal muscle adaptations that occur in response to the exercise stimulus. Endurance exercise induces adaptations in the cardiovascular system that allow an increase in capillary number and plasma volume expansion, supporting a greater surface area for gas exchange and the movement of blood, and thus enhancing oxygen transport to the active muscles [1]. Pronounced skeletal muscle adaptation to endurance exercise include an increase in mitochondrial content and size (mitochondrial biogenesis) and increased activity of oxidative enzymes, which collectively improve oxidative capacity [2, 3]. Accordingly, the capacity to perform daily work tasks can be improved as a consequence of endurance exercise.

Adaptation to exercise is thought to occur as a consequence of the accumulated response of acute exercise bouts, while nutrient availability can influence the acute response to exercise and may modulate chronic adaptations to exercise training [4]. Therefore, nutritional strategies provided in close temporal proximity to exercise have the potential to improve training efficiency by enhancing the magnitude of adaptations to the same training stimulus [5]. Emerging acute mechanistic evidence supports the potential benefit of post-exercise protein feeding in increasing muscle protein synthesis and mitigating proteolysis associated with an endurance exercise bout [6–8]. Cycling-based endurance training studies in 2009 and 2011 have also proposed the role of protein ingestion in supporting tolerance to intensified training in concurrence with an increase in the magnitude of training adaptations when repeated bouts of exercise are performed [9–11]. Taken together, post-endurance exercise protein intake may provide means to facilitate aerobic training adaptations. Nonetheless, the time course effects of prolonged post-exercise protein co-ingestion in enhancing the adaptive response to running-based endurance exercise training in adults remains to be established.

Protein synthesis is an outcome of a complex physiological process by which external stimuli, such as contractile activity and nutrient availability, promotes phenotypic characteristics in skeletal muscle [4]. It is becoming clear that both the exercise stimulus and protein feeding act independently and synergistically in modulating muscle protein synthesis, and consequently these subtle changes in muscle quantity or quality can mediate worthwhile training adaptations if sustained for weeks or months [4, 12]. Furthermore, protein ingestion during and following an acute endurance exercise bout has been shown to increase muscle protein synthesis and reduce muscle protein breakdown, and thus results in an increased whole body net protein balance [6, 13]. In spite of the fact that endurance exercise does not typically result in muscle mass accrual, the changes in muscle protein synthesis following endurance exercise are relevant to drive tissue repair and remodeling, in concurrence with the synthesis of non-contractile proteins, such as the mitochondria [14]. Indeed, acute and chronic endurance exercise has been demonstrated to stimulate the mitochondrial protein synthetic response [15, 16]. While the influence of protein ingestion on mitochondrial biogenesis machinery is not clear at present [8, 11, 17], its synthesis appears to be stimulated by the availability of extracellular amino acids in a dose-response manner [18]. This may infer that exogenous protein availability can enhance the capacity for muscular adaptations, although the role of post-exercise protein ingestion in enhancing the effects of running-based endurance exercise training remains largely unknown [11, 19].

Cardiovascular adaptations are a hallmark of endurance exercise training. An enhancement in oxidative capacity and maximal oxygen uptake () in response to aerobic training with post-exercise protein ingestion has been observed by some [10, 11], but not all [20] studies. In concordance, the role of protein feeding in enhancing the adaptive response to endurance training may not reside in the intramuscular milieu. Rather, noticeable cardiovascular improvements in  via an increase in plasma volume and plasma albumin content have been shown with protein ingestion [10, 11]. However, the addition of other nutrients such as caffeine, flavonoids, multivitamins and ribose [11, 20], in addition to the absence of macronutrient-specific comparisons by not including a carbohydrate-only supplement [10], makes it difficult to conclude whether these improvements in training adaptation are a result of protein intake *per se*. Interestingly, the magnitude of improvement in  during endurance training was greater when whey protein was ingested relative to a placebo [10], or when milk-based protein available in the form of chocolate milk was co-ingested, when compared to an energy-matched carbohydrate supplement and a placebo [11]. Collectively, these findings may infer nutrient-specific effects of post-exercise supplementation on endurance training adaptations.

In summary, recent scientific evidence from acute laboratory investigations and relatively extended cycling-based training studies supports the notion that nutrient intake can increase protein accretion and, ultimately, this may influence the magnitude of the training effect. This nutrient-exercise interaction may modulate the adaptive response to training and protein feeding appears to be an important factor in mediating this process. However, examining the long-term outcomes of these acute mechanistic models, particularly during free living endurance-type exercise, require further investigation. This project aims to address two issues (Phase I and Phase II). Phase I will address whether protein co-ingestion with carbohydrate immediately following exercise can increase the magnitude of cardiovascular and intramuscular training adaptations to endurance training when compared with ingestion of carbohydrate alone. Phase II while address to what extent the timing of protein co-ingestion (overnight versus immediate feeding) impacts upon those training adaptations.

It is hypothesized that the inclusion of protein in a post-exercise nutritional supplement will increase the magnitude of improvement in cardiovascular, but not intramuscular, adaptations following a long-term endurance training intervention in Phase I. Furthermore, it is hypothesized that overnight protein feeding will enhance the intramuscular adaptive response (markers of mitochondrial biogenesis) to endurance training relative to immediate feeding in Phase II.

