## Methods/Design

### Approach to research questions

The primary outcomes of this trial are the assessment of cardiovascular (changes in , plasma albumin content and plasma volume) and intramuscular (selected genes and proteins involved in cellular adaptive processes) training-induced adaptations, and whether protein co-ingestion (immediate or overnight) improves the magnitude of these adaptations. In accordance, two phases of testing will be conducted.

Phase I will be addressed by evaluating a carbohydrate-protein mixture against an energy-matched carbohydrate control to examine the influence of post-exercise protein intake in enhancing endurance training adaptations. Participants in Phase I will be randomly allocated to a group receiving an isocaloric carbohydrate supplement or a group receiving a carbohydrate-protein supplement, in a randomized investigator-participant double-blind manner, whereby the chief investigator ([name]) and participants will be blinded from the trial allocation. The acute post-exercise phase is important when considering the metabolic priority for recovery to be initiated [3, 21] and the potentiated sensitivity to nutritional interventions during this period [22]. It has been established that glycogen resynthesis and amino acid uptake rates are augmented following an exercise bout, and that the ingestion of carbohydrate and protein stimulate this process [6, 23–25]. This has subsequently prompted large numbers of studies to investigate the role of combined carbohydrate-protein ingestion in restoring glycogen stores, potential attenuation of decrements of skeletal muscle functional integrity and subsequent exercise performance [12, 26]. It is now generally accepted that incorporating protein into a post-exercise feeding regimen is a viable strategy to enhance recovery, mainly through observations in acute based studies [7, 8, 21, 27–33]. Yet, the effects of protein ingestion are more likely to be realized beyond the acute recovery phase, given that upregulation of endurance exercise-specific gene expression peaks between 10 and 24 hours following an exercise bout, and may surpass 96 hours for muscular recovery and adaptive remodeling to occur, suggesting that repeated bouts of exercise are required to detect worthwhile training adaptations [3, 34].

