### Experimental design

The proposed project involves two distinct phases of testing, each contrasting two nutritional interventions in a randomized investigator-participant double-blind parallel group design. The independent variable will be the precise nutritional intervention ingested following exercise in Phase I, while timing of ingestion will be the independent variable in Phase II. Specifically, those participants recruited for Phase I (n =32, approximately) of testing will receive a supplement containing carbohydrate (sucrose) plus protein (whey protein hydrolysate) at an ingestion rate of 0.4 and 0.4 g · kg BM^−1^ respectively. The second group will be a control group, whereby an ingestion of an isocaloric carbohydrate supplements will be assigned (0.8 g · kg BM^−1^). The two nutritional interventions provided in Phase II (n =32, approximately) will be identical (0.4 g · kg BM^−1^ carbohydrate +0.4 g · kg BM^−1^ whey protein hydrolysate), while the timing of intake will be manipulated. A group will ingest the carbohydrate-protein supplement immediately post-exercise and one hour later, while the overnight recovery group will receive the supplements one hour prior to sleep, and at 02:00, as an overnight nutritional intervention. The nutritional information for the supplements is provided in Table 1.

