### Sample size estimation

*A priori* sample size estimation (G*power version 3.1.7, University Düsseldorf, Düsseldorf, Germany) from data in the literature similar to the proposed work [11], revealed that a total of 24 participants are required to achieve 90% power to detect a worthwhile increase in an endurance performance () of 5.3 ml · kg^−1^ and standard deviation of 3.3 ml · kg^−1^, using a two-tailed t-test for independent means with an alpha level of 0.05. Rolling recruitment of 32 participants in each phase of testing will therefore be conducted when considering an anticipated 15% dropout rate [11, 36].

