### Data analysis

The majority of data include measurements of cardiovascular and intramuscular markers of endurance training adaptations at baseline and follow-up, and thus treatments × time interactions will be explored using a general linear model with baseline included as a covariate, to account for any baseline imbalances because of regression to the mean [62]. The majority of variables in this experiment therefore involve a single comparison between two level scores, and so will not be adjusted for multiple comparisons across the different variables. Any data that require a single comparison of two means will be tested for normality using the Shapiro-Wilk test before using an independent t-test or non-parametric equivalent to examine differences between treatment arms (for example, magnitude of change in absolute and relative  between treatments). Relationships between outcome variables will be examined using a Pearson’s product-moment correlation and any meaningful associations (r ≥0.7) between baseline, and the magnitude of response to exercise training will be further explored by post-stratification of the treatment group according to baseline status. Significance will be set at ≤0.05 and all results being reported as the mean and standard error of the mean (SEM) unless stated otherwise.

Participants will be advised at the initial trial enrollment meeting to carefully consider the required investment of time and effort involved in the current project. This will be undertaken to minimize any negative impact associated with loss to follow-up, and consequently likely withdrawal can be made prior to randomization [63]. However, any unforeseen circumstances or withdrawal resulting in loss to follow-up will be documented and reported in the final trial report. In accordance, the handling of missing data subsequent to withdrawal will be primarily approached in a complete-case analysis adjustment method, while an imputation method will be considered where appropriate [64, 65].

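### The only sample-size calculation concerns oxygen uptake, so it supports neither the Phase II intramuscular hypothesis nor the Phase I expectation of no intramuscular benefit

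*Protocol article*

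**What the plan says.** **Hypotheses (Background).** For Phase I, adding protein "will increase the magnitude of improvement in cardiovascular, but not intramuscular, adaptations following a long-term endurance training intervention in Phase I". For Phase II, "overnight protein feeding will enhance the intramuscular adaptive response (markers of mitochondrial biogenesis) to endurance training relative to immediate feeding in Phase II". No other hypothesis is stated for Phase II.

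**Outcomes (Approach to research questions).** The primary outcomes are cardiovascular and "intramuscular (selected genes and proteins involved in cellular adaptive processes) training-induced adaptations". Both families are primary for the trial as a whole.

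**Arms (Experimental design).** The two Phase II arms receive the same carbohydrate-protein supplement, "while the timing of intake will be manipulated".

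**Size (Sample size estimation).** The one calculation asks for 24 participants, at 90% power with a two-sided t-test at 0.05, "to detect a worthwhile increase in an endurance performance () of 5.3 ml"/kg with a "standard deviation of 3.3 ml"/kg. The outcome symbol was lost when the text was extracted. The units and context point to maximal oxygen uptake. The section then concludes: "Rolling recruitment of 32 participants in each phase of testing will therefore be conducted", citing 15% dropout.

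**Analysis (Data analysis).** A general linear model with baseline as covariate tests for treatment differences at 0.05, with "all results being reported as the mean and standard error of the mean (SEM) unless stated otherwise". No intramuscular effect size, SD or equivalence margin is given.

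**The concern.** A sample-size calculation supports a claim only when its endpoint and contrast are those of the claim. In Phase II neither matches the stated hypothesis. The endpoint is oxygen uptake rather than mitochondrial markers. The effect comes from a study that the Background describes as milk-based protein against energy-matched carbohydrate and placebo, not from a comparison of feeding times.

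Phase I has a different difficulty. Part of its hypothesis is that a co-primary family of outcomes will show no benefit. The planned tests look for differences. The only result they can return in line with that expectation is non-significance, which a small trial gives often even when a moderate effect exists.

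What is at stake is what the trial may conclude: whether a null Phase II result says anything about overnight feeding, and whether a null intramuscular result in Phase I can be read as no effect.

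**Working it through.** **1. The plan's own figure.** Inputs from Sample size estimation: difference 5.3, SD 3.3, two-sided alpha 0.05, independent t-test, 90% power. Equal allocation is assumed.

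- Standardized difference: d = 5.3/3.3 = 1.606.
- Power = P(T > t(0.975, 2n−2)), with T noncentral t on 2n−2 df and noncentrality d·√(n/2).
- n = 9 per arm: 89.2%. n = 10: 92.4%. n = 12: 96.4%.

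So 20 in total suffice for 90%, and the stated 24 gives about 96%. The dropout step does not reproduce either: 24/0.85 = 28.2, so 29, not 32. Both differences are on the safe side for oxygen uptake. With 32 recruited and 15% lost, 32 × 0.85 = 27.2, or about 27 completers (13 and 14 per arm).

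**2. Intramuscular difference detectable, unadjusted.** Solve the same power formula for d, in units of the marker's SD.

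| Completers | 90% power | 80% power |
|---|---|---|
| 24 (12/12) | 1.39 SD | 1.20 SD |
| 27 (13/14) | 1.30 SD | 1.12 SD |
| 32 (16/16) | 1.18 SD | 1.02 SD |

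**3. With the planned baseline adjustment.** A baseline–follow-up correlation r multiplies the residual SD by √(1−r²). The document gives no r, so 0.5 and 0.7 are assumed; the factors are 0.866 and 0.714. With 27 completers:

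- 90% power: 1.30 × 0.866 = 1.13 SD and 1.30 × 0.714 = 0.93 SD.
- 80% power: 1.12 × 0.866 = 0.97 SD and 1.12 × 0.714 = 0.80 SD.

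**4. What non-significance would mean in Phase I.** Assume a true intramuscular effect of 0.5 SD.

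- Unadjusted power is 22% at 12 per arm and 28% at 16 per arm, so 72–78% of such trials would be non-significant.
- With adjustment, the effective d is 0.5/√(1−r²) = 0.58 (r = 0.5) or 0.70 (r = 0.7), with one df lost to the covariate. Power is then 27–37% at 12 per arm and 35–48% at 16 per arm.
- Unadjusted 95% interval half-width, t(0.975, 2n−2)·√(2/n): 0.85 SD at 12 per arm and 0.72 SD at 16 per arm.

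**5. Could the size support equivalence?** The document sets no margin, so a range is shown. Two one-sided 5% tests, true difference zero, unadjusted, 200,000 simulated trials:

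| Assumed margin | 12 per arm | 16 per arm |
|---|---|---|
| 0.5 SD | 0.2% | 0.8% |
| 0.8 SD | 22% | 43% |
| 1.0 SD | 54% | 74% |

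**The case against.** Several points on the other side stand.

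- **Oxygen uptake is also primary in Phase II.** The cardiovascular outcomes are primary for the whole trial, and the Background says Phase II examines the effect of timing on the same adaptations. A reader might infer that the calculation is irrelevant to Phase II. It is not: the outcome applies, but the effect size does not come from a timing contrast and the calculation does not reach the intramuscular hypothesis.
- **The 90% is not claimed for the Phase II hypothesis.** A reader might infer that Phase II is presented as 90% powered for its own question. The text ties 90% to the 5.3 ml/kg difference; only the headcount is carried to each phase.
- **The Phase I wording may be an expectation.** The Background also poses Phase I openly, asking whether protein increases cardiovascular and intramuscular adaptations. The plan declares no equivalence objective and has no rule for reading non-significance as confirmation. The limited claim remains: the planned tests cannot lend that expectation much support.
- **A null intramuscular result is not automatic.** A 1.20 SD difference would be detected with 80% power at 12 per arm. The plan also names about 12 genes and proteins without multiplicity adjustment. If 12 tests were independent (an assumption), the chance of at least one false positive would be 1 − 0.95¹² = 46%.
- **Unadjusted figures and a single margin would overstate the problem.** Hence the ranges above.
- **Mean and SEM are only a default**, and a condensed article may leave interval reporting to a fuller plan. Intervals are therefore recommended as part of the remedy; their absence is not treated as an error.

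**Conclusion.** The point holds in this form: the headcount of each phase is justified only by an oxygen-uptake effect from a protein-versus-carbohydrate/placebo study. That does not support the Phase II hypothesis, which is intramuscular and compares the timing of one supplement. Nor does it let Phase I turn a non-significant intramuscular test into good evidence of no effect.

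With about 27 completers, the intramuscular difference detectable at 90% power is about 1.3 SD unadjusted, or about 0.9–1.1 SD adjusted. At 80% power it is about 1.1 SD, or 0.8–1.0 SD adjusted. These figures rest on equal allocation, 15% dropout, one marker tested at 0.05 and an assumed correlation of 0.7–0.5. The 22–28% power in Phase I rests on an assumed 0.5 SD effect and an unadjusted test.

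This does not show that the trial is underpowered for intramuscular markers, since no target effect is given and a large effect would be detected. It shows that the stated power does not cover them.

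**What to change.** 1. In Sample size estimation, state that the power calculation covers the oxygen-uptake contrast of Phase I only, and recompute it: the stated inputs give about 96% with 24, and 20 suffice for 90%.
2. For intramuscular markers in both phases, give the detectable difference with about 27 completers: about 1.3 SD (90%) or 1.1 SD (80%) unadjusted, and about 0.9–1.1 SD or 0.8–1.0 SD with baseline adjustment, naming the assumed correlation.
3. Describe the Phase II intramuscular comparison as not formally powered.
4. Report baseline-adjusted between-arm differences with 95% confidence intervals for the intramuscular outcomes, alongside the group means.
5. Word the Phase I statement on intramuscular adaptations as an expectation, and add that a non-significant result will not be reported as absence of effect.

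The cost is wording and one interval per outcome, with no extra participants. The downside is that the claims become more modest. By the Trial status section, Phase II recruitment was still to come, so its rationale could be corrected before it began.
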